### 3.6.3 Shipping of study drugs

Anakinra will be purchased locally at the Spitalpharmazie of the University Hospital Basel

### 3.6.4 Dosage, Preparation, Administration, and Storage

#### 3.6.4.1 Dosage

Each subject will receive one SC injections of study drug (100 mg anakinra or matching placebo) on visits 1, 2

#### 3.6.4.2 Preparation

Study drug will be prepared by a pharmacist or designated medical professional prior to administration.

#### 3.6.4.3 Administration

SC injections will be administered by a trained health care professional. Injections should be given in the anterior abdomen. The injection site will first be cleaned with an alcohol swab, and the alcohol will be allowed to dry prior to the injection.

On all study drug administration visits, all vital signs other than height and weight are recorded within 15 minutes prior to the injection, every 30  10 minutes following the injection until 3 hours after the injection, and immediately prior to the subject’s release. Subjects will not be discharged from the facility until at least 2 hours after the injection and at least 1 hour after vital signs are stable. If a subject experiences a serious adverse event (SAE), vital signs may be taken more frequently, per standard institutional practice. In the period following the injection, the responsible physician will be notified immediately should any of the following conditions apply:

- Systolic blood pressure is persistently (after 3 measurements) more than 20 mm Hg above or below baseline (dosing day, pre‑dose).
- Pulse is more than 20 beats per minute above or below baseline (dosing day, pre‑dose) or if pulse is irregular.
- Temperature is > 38.3C.
- Signs of anaphylaxis, including respiratory distress (dyspnea, oxygen desaturation with PO2 < 90% or onset of acute respiratory distress syndrome), flank or back pain, and/or hypotension. If any of these symptoms occur, appropriate therapy (e.g., oxygen, epinephrine, diphenhydramine, and corticosteroids) will be administered. Complete documentation of the event will be recorded.

#### 3.6.4.4 Storage and Handling

Study drug will be stored refrigerated at 2–8°C (36–46°F) and protected from direct sunlight until time of use. Aseptic techniques will be used during withdrawal, preparation, and administration.

Any study drug remaining in the vial once the subject’s dose has been prepared will not be discarded but will be stored in a secured area until a drug accountability has been performed.

#### 3.6.4.5 Drug Accountability

Anakinra/Kineret® and Placebo required for this study will be acquired commercially as mentioned in section 4.0. The site must maintain accurate records of all study drug received, dispensed, returned, or destroyed. Upon completion of the study, all study drug must be accounted for.

## 3.7 Selection of Doses Used in the Study

Subjects who receive active treatment will receive SC injections of 100 mg of anakinra . The rationale for the selected dose regimen is provided in Section 3.2.1.

## 3.8 Outcome Measures

### 3.8.1 Primary Outcome Measure

The primary endpoint is change in exercise-stimulated IL-6 between group dosed with placebo and anakinra.

### 3.8.2 Secondary Outcome Measures

The secondary endpoints are as follows:

- Change in glucose metabolism, insulin glucagon and GLP-1 secretion due to any treatment.
- Change of inflammatory markers (CRP, TNFα, IL-1Ra) due to any treatment.
- Change of stress hormones (cortisol, growth hormone, catecholamines) due to any treatment.
- Change of muscular enzymes (CK) due to any treatment.
- Well-being during and after exercise including muscle soreness due to any treatment.
- Activity Induced Fatigue (ACTIF) Scale before and after exercise due to any treatment.
- Depression
- Cognition
- Motor strength
- Change of vascular function (CAVI, PWV and AVR) due to any treatment.

The tests used to investigate the regulation of IL-6 during exercise are summarized in Table 3.

Table 3
Bloodanalysis

Blood samples will be drawn at the following time points: -60 min before, 0, 10, 20, 30, 40, 50, 60 min during exercise and at +10, +20, +30 and + 60 min after exercise.

A total of 250 ml blood will be drawn throughout the study.

The following parameters will be assessed:

| Time points: | -60 | 0 | 10 | 20 | 30 | 40 | 50 | 60 | +10 | +20 | +30 | +60 |
| --- | --- | --- | --- | --- | --- | --- | --- | --- | --- | --- | --- | --- |
|  | **before** | **exercise** | | | | | | | **after** | | | |
| IL-6 | x | x | x | x | X | x | x | x | x | x | x | x |
| GLP-1 (active) | x | x | x | x | X | x | x | x | x | x | x | x |
| Glucagon | x | x | x | x | X | x | x | x | x | x | x | x |
| Insulin | x | x | x | x | X | x | x | x | x | x | x | x |
| Glucose | x | x | x | x | X | x | x | x | x | x | x | x |
| IL-1Ra | x |  |  | x |  | x |  | x | x |  | x |  |
| GIP | x |  |  | x |  | x |  | x | x |  | x |  |
| usCRP | x |  |  | x |  | x |  | x | x |  | x |  |
| TNF-a | x |  |  | x |  | x |  | x | x |  | x |  |
| Cortisol | x |  |  | x |  | x |  | x | x |  | x |  |
| GH | x |  |  | x |  | x |  | x | x |  | x |  |
| CK | x |  |  |  |  |  |  | x |  |  |  | x |

### 3.8.3 Safety Outcome Measures

Safety will be assessed by the following outcome measures:

- AEs
- Clinically relevant abnormal changes in vital signs compared to baseline (Day 0 pre‑dose)
- Clinically relevant abnormal changes in laboratory values (hematology, chemistry, and urinalysis) compared to baseline (Day 0 pre‑dose)
- Dosing reactions (e.g., fevers, chills, relevant changes in vital signs, or hives within 4 hours of dosing)

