### 4.2.1 Screening Assessments (Day -28 to -7)

Subjects potentially meeting the inclusion criteria as determined over a pre-screening telephone call will be scheduled for their screening visit. The screening will take place 28 to 7 days prior to the first study procedure day. For the screening visit the selected subject will be given an appointment and instructed to come in after an overnight fast of 6-10 hours. If the subject fails to fast 6 – 10 hours prior to visit, appointment will be rescheduled to the next possible date. The following procedures and assessments will be conducted:

- Study investigators will obtain written informed consent before blood sampling from eligible subjects at the beginning of this same visit.
- Demographics (including age, sex and race)
- Medical history
- Concomitant medications
- Vital signs (heart rate, blood pressure (systolic/diastolic, measured 3 times), respiratory rate, temperature (oral or tympanic), s02, height, weight, BMI, medical history and a complete physical examination will be performed.
- Electrocardiogram (ECG)
- Complete blood count (CBC) with differential, platelets
- Serum chemistry including sodium, potassium, creatinine, CRP, liver transaminases, fasting plasma glucose, AP, CK
- Spontaneous urine sample (strip for the presence of protein, leucocytes and erythrocytes)
- Registration of right thigh (15cm above patella) and right upper arm (10cm above epicondylus lateralis) diameter in order to standardize muscle mass
- For subjects with reproductive potential, a willingness to use contraceptive measures adequate to prevent the subject’s partner from becoming pregnant during the study. Adequate contraceptive measures include hormonal methods used for two or more cycles prior to Screening (e.g., oral contraceptive pills, contraceptive patch, or contraceptive vaginal ring), double barrier methods (e.g., contraceptive sponge, diaphragm used in conjunction with contraceptive foam or jelly, and condom used in conjunction with contraceptive foam or jelly), intrauterine methods (IUD), sterilization (e.g., tubal ligation or a monogamous relationship with a vasectomized partner), and abstinence.
- Inclusion/exclusion
- A treadmill ergometer test will determine individual heart rate (HR)-VO2 relationships, and VO2max on which the exercise load for the acute exercise bout will be based (for further information see Appendix 1)

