#### 4.2.2.3 Visit 3 [Day 12 (9 Days)]

Subjects must fast for 6 to 10 hours prior to the clinic visit. If the subject fails to fast 6 – 10 hours prior to visit, appointment will be rescheduled to the next possible date. After all procedures for this visit have been completed, subjects should resume medications as previously prescribed.

The following procedures and assessments will be conducted:

- AEs
- Concomitant medications
- Muscle soreness
- Vital signs including pulse, blood pressure (systolic/diastolic), p02, respiratory rate, temperature (oral or tympanic), and weight (including calculation of BMI)
- Complete physical exam
- CBC with differential, platelets
- Serum chemistry including sodium, potassium, creatinine, CRP, liver transaminases, fasting plasma glucose, AP, CK
- Retrospective analysis blood sample

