## 5.2 Adverse Events

The occurrence of an AE will be determined based on observed or volunteered signs and symptoms, as well as changes in the subject’s physical examination and laboratory results. AEs that occur during the study will be recorded on the appropriate Adverse Event pages of the CRF.

An AE is defined as any untoward medical occurrence (e.g., sign, symptom, disease, syndrome, intercurrent illness, abnormal laboratory finding) that emerges or worsens relative to baseline (Day 0 pre-dose), regardless of the suspected cause. Untoward medical events that occur from the time the subject signs the informed consent form to the time the administration of the drug starts are not considered AEs, and should be recorded under medical history.

All AEs will be evaluated for their seriousness, severity, relationship to study drug, and outcome.

An AE occurring **at any dose** (including overdose) should be classified as **SERIOUS** if:

- It resulted in death (i.e., the AE caused or led to death).
- It was life threatening (i.e., the AE placed the subject at immediate risk of death; an AE should not be classified as life-threatening if it hypothetically might have caused death if it were more severe).
- It required or prolonged inpatient hospitalization (i.e., the AE required at least a 24‑hour inpatient hospitalization or prolonged a hospitalization beyond the expected length of stay; hospitalizations for elective medical/surgical procedures, scheduled treatments, or routine check-ups are not SAEs by this criterion).
- It was disabling (i.e., the AE resulted in a substantial disruption of the subject’s ability to carry out normal life functions).
- It resulted in a congenital anomaly/birth defect (i.e., an adverse outcome in a child or fetus of a subject exposed to the molecule or study drug prior to conception or during pregnancy).
- It does not meet any of the above criteria for a serious AE but may jeopardize the subject or may require medical or surgical intervention to prevent one of the outcomes listed above.

All AEs will be graded for severity according to the National Cancer Institute Common Terminology Criteria for Adverse Events (NCI CTCAE), version 3.0 (available on line at <http://ctep.cancer.gov/reporting/ctc.html>).

The following criteria will be used to assess whether there is a reasonable possibility that the study drug caused or contributed to the AE:

Yes (possibly, probably, or definitely related):

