## 6.5 Safety Analysis

Safety analyses will involve examination of the incidence, severity, and type of treatment‑emergent AEs reported, and changes in vital signs and laboratory test results from baseline (Day 0 pre-dose) to specified time points throughout the study.

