### 6.5.3 Vital Signs

For each assessment of vital signs, changes in vital signs from baseline (Day 0 pre-dose) will be summarized. Vital signs (including include pulse, blood pressure [systolic/diastolic], respiratory rate, temperature [oral or tympanic]), p02, body weight, height, and BMI will be summarized by treatment group and assessment time.

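### Laboratory safety change is measured from Day 0 pre-dose, but blood count, urinalysis and most chemistry have no Day 0 value and no sample between the two treatments

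*Protocol*

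**What the plan says.** Protocol section 3.8.3 lists as a safety outcome "Clinically relevant abnormal changes in laboratory values (hematology, chemistry, and urinalysis) compared to baseline" and gives the baseline as Day 0 before dosing. Section 6.5 carries this into the analysis: "changes in vital signs and laboratory test results from baseline (Day 0 pre-dose) to specified time points throughout the study". Section 5.3 uses the same reference point when it asks whether an abnormal result was already present at baseline. Section 5.1 lists urinalysis among the monitoring tests, and section 1.4 says that safety will be followed with blood and urine tests.

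The schedule is narrower. Section 4.2.1 (screening, Day -28 to -7) has "Complete blood count (CBC) with differential, platelets", a chemistry panel and a urine strip. Section 4.2.2.3 (Visit 3) has "CBC with differential, platelets" and "Serum chemistry including sodium, potassium, creatinine, CRP, liver transaminases, fasting plasma glucose, AP, CK", but no urine. The lists for Visits 1 and 2 (sections 4.2.2.1 and 4.2.2.2) contain none of the three. Appendix 2a agrees: blood count and serum chemistry at screening and Visit 3, urinalysis at screening only.

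**The concern.** The outcome is defined against a measurement that the schedule does not contain. An analysis plan can relabel the baseline, but it cannot supply a missing sample.

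There is a second and larger difficulty. In this crossover each man receives anakinra at one of Visits 1 and 2 and placebo at the other. A laboratory test taken once before both and once after both shows what happened over the whole study, not what happened under either treatment. Section 1.4 names a fall in white cells as an effect consistent with how anakinra works and links it to infection risk. The blood count is therefore the test for which a reader would most want a comparison with placebo.

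**Working it through.** No stated figure is at issue, so the check sets the schedule beside the outcome definition.

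**Step 1. Which tests have a Day 0 pre-dose value?** Sources: sections 4.2.1, 4.2.2.1 to 4.2.2.3, Tables 3 and 5, Appendix 2a.

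| Test | Screening | Visit 1 pre-dose (Day 0) | Visit 2 pre-dose | Visit 3 |
| --- | --- | --- | --- | --- |
| Blood count | yes | no | no | yes |
| Sodium, potassium, creatinine, transaminases, AP | yes | no | no | yes |
| Glucose, CRP, CK | yes | yes (-60 min) | yes (-60 min) | yes |
| Urine strip | yes | no | no | no |

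Table 5 puts the -60 min sample before the injection, so glucose, CRP and CK do have the named baseline. They are also sampled after dosing at each visit (Table 3). For the other rows the scheduled Day 0 count is 0 of 20 men.

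**Step 2. Can a change be assigned to a treatment?** For the blood count and the five other chemistry items, let m be the untreated mean, a the change after anakinra and p the change after placebo.

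- Screening: m, coefficients (1, 0, 0).
- Visit 3, either sequence: m + a + p, coefficients (1, 1, 1).

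These rows have rank 2 for 3 parameters. Only the sum a + p can be estimated. Comparing the two sequences at Visit 3 shows the effect of treatment order and of time since each dose, not anakinra against placebo.

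**Step 3. How far from the anakinra dose is the only post-dose sample?** Section 3.1 separates visits by 72 hours to 9 days. Group 1 (anakinra at Visit 1) is two gaps away: 2 × 3 = 6 to 2 × 9 = 18 days. Group 2 (anakinra at Visit 2) is one gap away: 3 to 9 days. The Appendix 2a windows (Visit 2 on Days 6 to 9, Visit 3 on Days 12 to 18) put Group 1 at 12 to 18 days. The Visit 3 window in the heading of section 4.2.2.3 differs again. None of these readings changes Step 2.

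**Step 4. Urinalysis.** There are no scheduled post-dose values, so no change exists under any baseline.

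**Step 5. Does an added pre-dose sample at Visits 1 and 2 repair this?** Day 0 gives (1, 0, 0). Visit 2 pre-dose gives (1, 1, 0) in Group 1 and (1, 0, 1) in Group 2. Visit 3 gives (1, 1, 1). The rank is now 3 of 3. Allowing also for a period effect, half the between-sequence difference in (period 1 change minus period 2 change) estimates a - p, provided the first treatment does not carry over. Renaming the baseline alone leaves the rank at 2.

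**The case against.** **Safety is secondary and exploratory.** The objective is IL-6 regulation, section 6.0 announces mainly descriptive statistics, and section 6.5.2 promises only that laboratory results are tabulated and out-of-range values reported. No laboratory table by treatment is planned. This stands and limits the weight of the point. It does not supply the baseline that sections 3.8.3, 5.3 and 6.5 require.

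**Stored blood could fill the gap.** A retrospective-analysis sample is listed before dosing at Visits 1 and 2. Plasma might yield some chemistry later, but the protocol gives that sample no safety use, and centrifuged plasma cannot give a blood count.

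**Few white-cell events are expected.** If the 2.4% in section 1.4 applied to one dose in healthy men, which is an assumption, 20 × 0.024 = 0.48 cases would be expected, and the chance of none would be 0.976^20 = 0.62. Nor do the documents show that a count taken 3 to 9 days after a single dose would still reveal a fall. This stands: the added sample makes attribution possible but does not give power.

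**A reader might infer that vital-sign and adverse-event effects are equally confounded.** Section 6.5.3 says that "changes in vital signs from baseline (Day 0 pre-dose) will be summarized", which applies Day 0 to Visit 2 as well. The documents do not support that reading:

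- Vital signs are recorded around the injection at both visits. With a common baseline B, (Y1 - B) - (Y2 - B) = Y1 - Y2, so the within-man contrast is unchanged. With 10 men per sequence, each treatment mean also contains both periods equally.
- A visit-specific baseline would add noise under assumed inputs (within-man SD 5, independent errors, no carryover). The standard error of the contrast is √(2 × 25 × 2/10)/2 = 1.58 with the common baseline and √(4 × 25 × 2/10)/2 = 2.24 with the visit-specific one. A simulation of 4,000 runs gave 1.57 and 2.20, both unbiased.
- The dosing-day reference in section 3.6.4.3 is a trigger for notifying the physician, not a competing analysis baseline.
- Section 5.2 defines an adverse event as one "that emerges or worsens relative to baseline (Day 0 pre-dose), regardless of the suspected cause". Nothing says that a period 1 event is counted again under the second treatment. Events are assessed 24, 48 and 72 hours after each bout (section 5.4), and Appendix 4 records onset and duration.

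**Conclusion.** The point holds for the blood count, urinalysis, sodium, potassium, creatinine, transaminases and AP. For these, 0 of 20 men have the baseline that the protocol names. For the blood count and the listed chemistry, the only scheduled post-dose sample in a completer follows both treatments, so the treatment effects cannot be separated. For urinalysis no change can be computed. A man who stops after one dose would have an early-termination blood count and panel (section 4.2.2.4), but that offers no planned comparison.

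The loss of attribution comes from the single late sample; the baseline wording is a separate error. It would be wrong to say that no chemistry has a Day 0 value, or that the trial cannot separate anakinra and placebo on safety in general. Glucose, CRP, CK, vital signs and adverse events are all collected in both periods. The primary endpoint is untouched. This is a correction that should be made, because a stated safety outcome cannot be delivered as written.

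**What to change.** Preferred: add the blood count and the missing chemistry (sodium, potassium, creatinine, transaminases, AP) to the -60 min draw at Visits 1 and 2, and enter them in sections 4.2.2.1 and 4.2.2.2 and in Appendix 2a. Day 0 then exists as the baseline, Visit 2 pre-dose closes period 1 and Visit 3 closes period 2. The cost is a few routine tubes per man from a catheter already in place, on top of the stated 250 ml, which would need updating. The protocol gives no tube volumes, so the exact addition is not computed here.

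If no samples are added: name screening as the laboratory baseline in sections 3.8.3, 5.3 and 6.5, and state that Visit 3 laboratory changes reflect both treatments together. This costs only wording. It removes the contradiction but does not restore attribution.

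In either case, add a urine strip at Visit 3 or remove urinalysis from sections 3.8.3 and 5.1. A Visit 3 strip would be read against screening, since Day 0 has none, and would also reflect both treatments. No change is needed to the vital-sign or adverse-event baseline on this account.

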## 3.9 Subject costs and insurance

All assessments mentioned in this protocol as well as the study drugs are free of charge for the subject. This study will not cause personal or insurance related costs. In case of damage all research subjects are covered by the University Hospital Basel.

## 3.10 Subject Compensation

All subjects will be given financial compensation according to table 4

Table 4
Subject Compensation

| ***Visit*** | *0 (screen)* | *1* | *2* | *3* |
| --- | --- | --- | --- | --- |
| **Payment in SFR.** | 20 | 90 | 90 | 30 |

## 3.11 Financing

The study will be financed by the SNF.

# 4.0 STUDY OPERATIONS and Evaluations

[name] at the University Hospital Basel both the principal investigator and sponsor of this trial. [name] is supplying Anakinra/Kineret®, which is commercially available.

## 4.1 Reporting and Recording of Data

The CRFs will be completed according International Conference on Harmonization/Good Clinical Practice (ICH/GCP) Guidelines.

A CRF will be completed for each subject enrolled under this protocol. Information collected on the subjects who fail screening will include date of birth, and the reason the subject was not enrolled.

All information collected in the CRF will be verifiable in the source documents. Source documents for this trial will include any study-specific worksheets or laboratory result reporting documents. Subject medical records will contain reference to the study title and assigned subject identification number. The signed consent form will be filed with the subject’s medical record.

CRF completion will be kept current to reflect subject status during the course of the trial. All CRF data will be reviewed, signed, and dated by the principal investigator.

Study subjects will be identified by subject ID number and date of birth.

## 4.2 Study Assessments

Study assessments are shown in the Schedule of Assessments (Appendix 2). Routine laboratory analyses, including chemistries, complete blood count (CBC), coagulation measures, urinalysis, and diabetes-specific analyses will be performed locally.

### 4.2.1 Screening Assessments (Day -28 to -7)

Subjects potentially meeting the inclusion criteria as determined over a pre-screening telephone call will be scheduled for their screening visit. The screening will take place 28 to 7 days prior to the first study procedure day. For the screening visit the selected subject will be given an appointment and instructed to come in after an overnight fast of 6-10 hours. If the subject fails to fast 6 – 10 hours prior to visit, appointment will be rescheduled to the next possible date. The following procedures and assessments will be conducted:

- Study investigators will obtain written informed consent before blood sampling from eligible subjects at the beginning of this same visit.
- Demographics (including age, sex and race)
- Medical history
- Concomitant medications
- Vital signs (heart rate, blood pressure (systolic/diastolic, measured 3 times), respiratory rate, temperature (oral or tympanic), s02, height, weight, BMI, medical history and a complete physical examination will be performed.
- Electrocardiogram (ECG)
- Complete blood count (CBC) with differential, platelets
- Serum chemistry including sodium, potassium, creatinine, CRP, liver transaminases, fasting plasma glucose, AP, CK
- Spontaneous urine sample (strip for the presence of protein, leucocytes and erythrocytes)
- Registration of right thigh (15cm above patella) and right upper arm (10cm above epicondylus lateralis) diameter in order to standardize muscle mass
- For subjects with reproductive potential, a willingness to use contraceptive measures adequate to prevent the subject’s partner from becoming pregnant during the study. Adequate contraceptive measures include hormonal methods used for two or more cycles prior to Screening (e.g., oral contraceptive pills, contraceptive patch, or contraceptive vaginal ring), double barrier methods (e.g., contraceptive sponge, diaphragm used in conjunction with contraceptive foam or jelly, and condom used in conjunction with contraceptive foam or jelly), intrauterine methods (IUD), sterilization (e.g., tubal ligation or a monogamous relationship with a vasectomized partner), and abstinence.
- Inclusion/exclusion
- A treadmill ergometer test will determine individual heart rate (HR)-VO2 relationships, and VO2max on which the exercise load for the acute exercise bout will be based (for further information see Appendix 1)

